### Additional analyses – CT scans

All rotational profile measurements will be performed at NNUH under standard operating procedure on a full diagnostic workstation (Synapse DICOM viewer, Fujifilm, Japan; High resolution 2 K monitors, Radiforce RX340, Eizo, Mönchengladbach, Germany) in the bioimaging laboratory and under the supervision of a consultant musculoskeletal radiologist (AT).

### Reproducibility

Inter-rater reliability will be assessed using intra-class correlation coefficients and 95% limits of agreement derived from Bland-Altman plots.

### TKR alignment versus native landmarks

The difference between the post-operative component rotational alignment and the pre-operative native landmarks will be assessed using Bland-Altman plots.

### Correlation with PROMS

The correlation between the PROMs and the difference between the post-operative component rotational alignment and the pre-operative native landmarks will be assessed using a correlation coefficient. A regression model will also be fitted including the randomisation group to allow for a potential between-group difference in PROMs.

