## Introduction

### Background and rationale

Osteoarthritis of the knee is a common musculoskeletal condition. The surgical management of painful, end-stage osteoarthritis is by total knee replacement (TKR) which should be considered before there is prolonged and established functional limitation and severe pain [1]. Over 100,000 TKRs were performed in the UK in 2019 [2]. While TKR frequently reduces pain and improves physical function in the majority of patients, 20% of patients report poor functional outcomes post-operatively [3, 4]. Such poor outcomes are of importance to patients and have a considerable financial and service-provision impact on NHS care. Research is needed to improve post-arthroplasty outcomes for those patients.

There is a paucity of literature regarding the kinematic outcomes of patients following TKR. However, there is uncertainty as to whether good Patient-reported Outcome Measures (PROMs) are associated with a return to normal kinematics of the TKR knee compared to the native knee. Movement analysis can be used to examine the change in kinematics before and after TKR by examining functional movements in activities of daily living.

The long-term success of TKR depends largely on correct component alignment and accurate ligamentous balancing [5]. The impact of femoral- and tibial-component rotation on flexion-gap balance, patellofemoral tracking and normal kinematic function is well-known [6–8]. Complications secondary to poor component alignment have been reported to lead to a higher rate of revision surgery [9, 10]. Computerised tomography (CT) imaging is a valid and reproducible technique for accurately measuring TKR-component rotation [11, 12]. However, despite CT being widely used to examine implant rotation, the correlation between rotational alignment, PROMs and kinematic function comparing pre- and post-operative measurement is unclear [13, 14]. It is hypothesised that patients with poor rotational profile post-operatively compared to their pre-operative values will have significantly worse PROMs, movement parameters and patient satisfaction.

We report the protocol of a two-group, parallel randomised controlled trial (RCT) comparing patient-reported, surgical and biomechanical outcomes from a TKR of a newer design (the JOURNEY II Bi-Cruciate Stabilised knee arthroplasty (BCS)) designed to provide improved kinematic outcomes compared to an older design TKR implant (the GENESIS II).

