### Aims

The principal aim of the trial is to compare the change in PROMs scores of the JOURNEY II BCS knee and the GENESIS II knee from pre-operation to 6 months post operation. Additional aims are as follows:
To determine whether the temporal and spatial parameters of gait, the range of movement and static and dynamic balance are closer to aged-matched normative data in those receiving the JOURNEY II BCS compared to those receiving the GENESIS II kneeTo monitor the change in function (Aim 1 above) and PROMs of the JOURNEY II BCS and the GENESIS II knee from post operation to 6 months post operationFrom CT scan measures, determine anatomical landmarks and rotational profile around the native knee and following TKR to ascertain the component rotational position post-operatively compared to anatomical landmarksTo examine the relationship between rotational values determined by CT scanning with pre- and post-operative PROMs and movement analysisTo develop knowledge and understanding of patient and surgeon experiences, perspectives and satisfaction when receiving or implanting the JOURNEY II BCS compared with the GENESIS II knee, and their experiences of recovery and rehabilitation

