### Statistical analysis

A full Statistical Analysis Plan (SAP) will be developed between the trial statistician and chief investigators and agreed with the trial’s Governance Committees. All analysis will be based on the intention-to-treat principle in which all participants will be analysed according to the group to which they were allocated, regardless of compliance.

Baseline factors will be summarised by group. All continuous variables will be summarised by the mean and SD, or if appropriate, the median and interquartile range. Categorical variables will be summarised with the number and percentage, in each category.

The primary comparison for OKS will be made using a general linear model with the stratification factors included as fixed effects. The difference between arms will be summarised using the mean difference, with 95% confidence intervals presented. A similar analysis will be undertaken for all other outcome measures.

For the temporal gait parameters and kinematic outcomes, each participant’s ‘closeness’ to age-matched normative data will be calculated. This will then be compared between groups using a general linear model with the stratification factors included as fixed effects. This data will also be presented graphically via scatter and distributional graphs to describe the deviations from the normative data.

For all the measures of movement listed, a general linear model with the stratification factors included as fixed-effects will be used to assess for between-group differences. If appropriate, adjusted analyses will be undertaken by including baseline factors and fixed effects in the above models.

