### Correlation with movement analysis

A similar analysis will be undertaken for the correlation between movement analysis and the difference between the post-operative component alignment and the pre-operative native landmarks.

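### The alignment regressions name randomised arm as their one covariate, which cannot remove confounding of the component-minus-native difference by pre-operative status

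*Protocol article*

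**What the plan says.** All references are to the protocol article.

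- **Exposure** (section *Correlation with PROMS*). The quantity correlated is given as "The correlation between the PROMs and the difference between the post-operative component rotational alignment and the pre-operative native landmarks". In short, D = C − N, with C the component rotation and N the native rotation.
- **Models** (same section). A correlation coefficient comes first, then: "A regression model will also be fitted including the randomisation group to allow for a potential between-group difference in PROMs". Arm is the only covariate named, and the reason given for it is a difference in outcome between arms.
- **Movement outcomes** (section *Correlation with movement analysis*). "A similar analysis will be undertaken for the correlation between movement analysis and the difference" shows that the same approach carries over.
- **Hypothesis** (section *Background and rationale*). Patients with "poor rotational profile post-operatively compared to their pre-operative values will have significantly worse PROMs", with movement and satisfaction named as well.
- **Aim** (section *Aims*). The CT aim is to "examine the relationship between rotational values determined by CT scanning with pre- and post-operative PROMs", and movement analysis is included.
- **Other adjustment text.** Section *Statistical analysis* says: "If appropriate, adjusted analyses will be undertaken by including baseline factors and fixed effects in the above models". The CT analyses come after that sentence. Section *Assumptions and sensitivity analysis* allows adjustment for factors that are imbalanced between the randomised groups.

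**The concern.** D is observed, not assigned. One of its two parts is the patient's native anatomy, measured before surgery. The CT aim looks at rotation against pre-operative as well as post-operative scores, so the protocol treats a link between native rotation and pre-operative status as an open question. If that link exists and patients who start worse also tend to finish worse, D and the 6-month outcome share a cause that has nothing to do with how the component was placed.

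The one covariate named does not address this. Randomisation makes arm independent of native anatomy and pre-operative status in expectation, so conditioning on it leaves the shared cause in place. The between-arm models in section *Statistical analysis* at least carry the stratification factors; the alignment regression does not name them.

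At stake is the directional hypothesis in the background section. A spurious association could be read as supporting it, or a real one could be masked.

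**Working it through.** **Where n = 72 comes from.** Section *Sample size* gives a difference of 5, SD 7.4, 80% power and 10% dropout. It states no alpha; two-sided 5% is assumed here. The normal approximation gives 2 × (1.960 + 0.842)² × (7.4/5)² = 34.4, so 35 per arm. The t-based calculation gives 35.4, so 36 per arm, 72 in all, and 72/0.9 = 80. The stated 80 is reproduced, and 72 is the number expected to be analysed.

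**Inputs the documents do not give (all assumed).** SD(N) = 6 degrees; SD(C) = 4 degrees; corr(C, N) = ρ = 0.2; a = corr(N, pre-operative score) from 0.2 to 0.4; b = corr(pre-operative score, 6-month score) from 0.4 to 0.6; no true effect of component position.

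**Step 1: how strongly D carries N.**
corr(N, D) = (ρ·SD(N)·SD(C) − SD(N)²) / (SD(N)·SD(D))
SD(D)² = 36 + 16 − 2 × 0.2 × 24 = 42.4
corr(N, D) = (4.8 − 36) / (6 × √42.4) = −0.80

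**Step 2: spurious correlation with outcome.** With no effect of position, corr(Y, D) = a × b × corr(N, D).
- a = 0.2, b = 0.4: −0.06
- a = 0.3, b = 0.5: −0.12
- a = 0.4, b = 0.6: −0.19

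Rough check of the middle case by Fisher's z: 0.1206 × √69 = 1.00, so the two-sided 5% test rejects with probability of about 0.17.

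**Step 3: simulated false-positive rates, n = 72.**

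| a, b | Signed D, arm only | Signed D, arm + pre-operative score | Absolute D, arm only, no mean offset |
|---|---|---|---|
| 0.2, 0.4 | about 8% | about 5% | about 5% |
| 0.3, 0.5 | about 17% | about 5% | about 5% |
| 0.4, 0.6 | about 37% | about 5% | about 6% |

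If C is offset from N by 3 degrees on average, the absolute-mismatch rates rise to about 6%, 9% and 14%.

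**Step 4: when the bias vanishes.** It is nil if a = 0, if b = 0, or if ρ·SD(C) = SD(N), because D is then uncorrelated with N. With equal SDs and ρ = 0.8 it is small: 7.7% at a = 0.3, b = 0.5. With component SD half the native SD, ρ = 0, a = 0.5 and b = 0.6, it reaches 62.9%.

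**Step 5: what each covariate costs.** In the middle case the standard error of the slope on D is about 0.0184 with arm only and 0.0167 once the pre-operative score is added. Adding N as well multiplies the latter by about 1.6; the variance inflation from corr(N, D) = −0.80 is 1/(1 − 0.64) ≈ 2.8. Also, β(C − N) + γN = βC + (γ − β)N. With N in a linear model, the coefficient on D is therefore the coefficient on component position.

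**The case against.** **Arm is the only covariate named, not the only one allowed.** The text says the regression includes arm; it does not exclude other terms, and a statistical analysis plan is promised before comparative analysis. This stands as a limit on wording. The point survives because the article does more than stay silent: it fixes the exposure, names one covariate and gives its reason, and that covariate does not meet the main threat. The two general adjustment clauses do not clearly reach this analysis. One is optional and refers to models placed above it; the other concerns imbalance between arms.

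**The language is of correlation, not effect.** This is largely right. The aim and both section headings speak of relationship or correlation, and no recommendation on component placement is planned. Only the background hypothesis is directional. Looking at pre-operative scores, as the aim intends, could also reveal the confounding.

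**Signed or absolute?** The hypothesis about a poor profile suggests size of mismatch, and the article does not say which is meant. For absolute mismatch with no mean offset the problem nearly disappears. This stands, and the rates must be read with it.

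A reader might infer two stronger conclusions that the documents do not support:

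- *Any link between native anatomy and pre-operative state will show up as an effect of malrotation.* Step 4 shows that two further conditions are needed and that the bias can be nil.
- *Native angle must go into the lead model.* Under the assumed mechanism the pre-operative score alone restores about 5%. Native angle widens the interval substantially and turns the coefficient into that of component position, whereas the protocol asks about mismatch to native.

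**Conclusion.** The concern holds in limited form. The planned alignment regressions relate outcome to a non-randomised difference, and the one adjustment they name cannot remove confounding by pre-operative status. Whether this biases the result, and by how much, cannot be determined from the protocol. The range of about 8% to 37% false positives is for the signed difference and rests on assumed SDs and correlations; for absolute mismatch with no mean offset it is about 5% to 6%. It also assumes that the outcome is the 6-month score, since the article does not say whether scores or changes are meant. The analysis is secondary and observational, and the randomised comparison of the Oxford Knee Score is untouched.

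**What to change.** In sections *Correlation with PROMS* and *Correlation with movement analysis*, or in the analysis plan that implements them:

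1. Make the lead analysis a regression of the 6-month outcome on the component-minus-native difference, with implant arm, the pre-operative value of the same outcome, site and age stratum as covariates.
2. State whether the difference is signed or absolute.
3. Report the raw correlation as descriptive.
4. Use a model that also includes native angle as a sensitivity analysis at most, and say that its coefficient is that of component position.

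Site and age stratum are included for consistency with the trial's other models; the simulation does not test them.

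**Cost.** This is a change of wording, with three more degrees of freedom out of about 72. Site and age are recorded for stratification, and baseline measures are taken before surgery. If a particular measure has no pre-operative value, the plan should name the baseline measure that stands in for it. Under the assumed inputs, adding the pre-operative score slightly reduces the standard error, so precision is not lost.

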### Correlation with movement analysis

A similar analysis will be undertaken for the correlation between movement analysis and the difference between the post-operative component alignment and the pre-operative native landmarks.

### Additional analyses – qualitative study

Interview transcripts will be organised using NVivo qualitative data management software (QSR International, Burlington, MA, USA). Analysis will follow qualitative content analysis procedures [42]. Coding and thematic analysis will be carried out independently by two experienced qualitative researchers. Trustworthiness strategies [43] will be used to increase the credibility, dependability and transferability of analysis and interpretation. This will include cross-checking and review of codes and themes; constant comparative method (hypothesis testing within and across the dataset) and deviant case analysis (the use of ‘outliers’ as a resource for understanding and interpretation of data) [44].

### Analysis population and missing data

The analysis population is defined as:
Intention-to-treat: all randomised individualsPer-protocol: all randomised individuals who do not have an alternative TKR during the follow-up period. Individuals will be included up to the point of the alternative TKRSafety population: all randomised individuals who receive the TKR

Missing outcome data will be multiple imputed to increase precision of the treatment effect estimates. Sensitivity analyses will be conducted to assess the impact of the multiple imputations and a complete case analysis will also be conducted. All imputations will be examined to ensure that sensible values are being generated. Imputation models will contain baseline measures, outcome measures and factors predictive of missing data.

No interim analysis is planned for this study.

## Methods: monitoring

### Data monitoring

A TMG has been convened to assist with developing the design, co-ordination and strategic management of the trial. A Safety Committee will review safety data and act in place of a Data Monitoring Committee (DMC). Monitoring activities will be undertaken both centrally and on site. The frequency, type and intensity of routine and triggered monitoring are detailed in the Quality Management and Monitoring Plan (QMMP). Ongoing central monitoring will ensure quality and consistency of data thorough the trial. Details about data collection and cleaning are described in the Data Management Plan (DMP).

### Harms

#### Safety

Definitions of harm of the EU Directive 2001/20/EC Article 2 based on the principles of International Council for Harmonisation (ICH) guideline for Good Clinical Practice (GCP) apply to this trial. A record of all study-related SAEs, including details of the nature, onset, duration, severity, relationship to the device, relationship to the operative procedure, outcome and expectedness will be made on the relevant section(s) of the trial-specific SAE Form to be sent to the trial manager for onward reporting where required. SAEs resulting from surgery or arthroplasty complications (clinical and safety outcomes) will be reported in the relevant section of the Case Report Form (CRF).

All non-serious AEs and adverse drug events (ADEs), whether expected or not, should be recorded in the participant’s medical notes and also reported in the relevant section of the CRF.

Adverse events do *not include*:
Readmissions for revision surgeryMild (i.e. not lasting for more than 5 days) anaesthetic-related complications: nausea, vomiting, dizziness, drowsiness, vaso-vagal drop, hypotension and constipationMedical or surgical procedures; the condition that led to the procedure is the AEPre-existing disease or a condition present that was diagnosed before trial entry and does not worsenHospitalisation where no untoward or unintended response has occurred, e.g. elective surgery, social admissions

The Safety Committee will be provided with safety data for each treatment arm including related AEs. The Committee will advise on the continuation or early stoppage of the trial in the unlikely event that there are concerns over harm to participants. The medical care in response to any harm from the trial participation will be managed by routine NHS care.

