#### Secondary outcomes: clinical efficacy outcomes

Clinical efficacy will be evaluated by:
Surgical-related parameters: need for revision surgery; length of hospital stay and change in pain medication will be collected during in-patient stay and at all the follow-up time pointsPerformance-related parameters: knee flexion and extension ranges of movement, measured at 6 to 8 weeks and 6 months post-operatively by the research associate in the MoveExLab (and by the research physiotherapist at baseline as part of routine care); timed-up-and-go (TUG) [32] and timed 6-minute walk test [33] recorded at the 6–8 week and 6-month time points by the research associate in the MoveExLab

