### Blinding (masking)

It is not possible to blind the surgeon to the trial intervention. However, the participants, the physiotherapists and all staff involved in assessing outcomes will be blinded. Processes will be in place to maintain blinding. These will include concealment in a sealed envelope of the surgery notes mentioning the prosthesis implanted in the patient file.

In the unlikely event of a research nurse accidentally becoming unmasked, the contacts, assessments and data entry for that participant will be undertaken by another member of the research team for the remaining period of trial participation for that participant. Accidental unmasking will be logged and monitored to ensure that the appropriate steps are taken to prevent a re-occurrence.

The clinical staff providing usual care will also be blinded. The decision to unmask a case will be made when knowledge of an individual’s allocated treatment is required to enable treatment of a serious adverse event (SAE) which is likely to be caused by the type of device implanted.

Where possible, requests for emergency unmasking of individuals will be made via the trial manager in agreement with the clinical chief investigator. However, in circumstances where there is insufficient time to make this request or for agreement to be sought, the treating clinician can make the decision to unmask immediately. This can be done via the trial database.

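### The SAE Form takes only study-related SAEs, so serious events are captured more narrowly than non-serious ones and the by-arm safety data may be incomplete

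*Protocol article*

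**What the plan says.** The Safety section (under Harms) sets three recording rules.

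- **SAE Form.** It is to hold "A record of all study-related SAEs, including details of the nature, onset, duration, severity, relationship to the device, relationship to the operative procedure", among other details, and goes to the trial manager for onward reporting where required.
- **SAEs on the Case Report Form.** "SAEs resulting from surgery or arthroplasty complications (clinical and safety outcomes) will be reported in the relevant section of the Case Report Form (CRF").
- **Non-serious events.** "All non-serious AEs and adverse drug events (ADEs), whether expected or not, should be recorded in the participant’s medical notes" and also on the Case Report Form.

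The section then says how the data are used: "The Safety Committee will be provided with safety data for each treatment arm including related AEs". The Committee advises on continuing or stopping early, and under Data monitoring it acts in place of a Data Monitoring Committee.

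On masking, the Blinding section says "It is not possible to blind the surgeon to the trial intervention", but also that "the participants, the physiotherapists and all staff involved in assessing outcomes will be blinded". Staff giving usual care are blinded too. The article does not say who decides that an SAE is study-related.

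**The concern.** Safety data are normally collected first and attributed afterwards, so that a causal opinion cannot remove an event from the record. Here the order is reversed for serious events: someone must call an SAE study-related before it reaches the form whose fields ask about its relationship to the device and to the operation. Non-serious events face no such test, so the more important class of event has the narrower net.

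What is at stake is how complete the by-arm safety picture is. An SAE thought unrelated at the time cannot be reconsidered later if it was never written down, for example when a pattern emerges in one arm. With 80 patients, SAE counts are likely to be small, so a few missing events could change what the Committee sees.

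**Working it through.** The article gives no SAE rate and no proportion judged related, so there is no plan figure to reproduce. The check is mainly a comparison of the stated capture routes.

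| Route (section) | Limited by cause? |
|---|---|
| SAE Form (Safety) | Yes: study-related only |
| SAEs on the Case Report Form (Safety) | Yes: must result from surgery or arthroplasty complications |
| Non-serious AEs and ADEs (Safety) | No: all; the only qualifier concerns expectedness |
| Notes review (clinical safety outcomes) | Yes: complications related to the surgery |
| Additional-treatment question at each visit (clinical safety outcomes) | No, but it asks about treatment received |
| Revision surgery (clinical efficacy outcomes) | No, but it covers one type of event |

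**Step 1. Follow a serious event judged unrelated.** It fails the entry condition of the SAE Form and of the Case Report Form route. The non-serious rule does not apply to it. The notes review takes only surgery-related complications. The visit question may reveal that treatment was given, but the article does not say that it yields an SAE record with onset, severity and causality. Revision has its own outcome ("need for revision surgery; length of hospital stay and change in pain medication will be collected during in-patient stay" and at follow-up), which matters because readmission for revision is excluded from the definition of an adverse event. No route is stated that records this event as an SAE.

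**Step 2. Compare with a non-serious event of the same cause.** The rule begins "All non-serious AEs and adverse drug events (ADEs), whether expected or not, should be recorded", with no causal condition, so the minor event is kept.

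**Step 3. Follow the data to the Committee.** It receives safety data by arm. Those data can extend beyond related events only as far as unrelated events have been recorded somewhere.

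**Step 4. Size, by assumption only.** Eighty patients at 1:1 gives about 40 per arm. Let p be the true SAE risk and c the proportion that passes the filter.

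- Expected SAEs per arm = 40 × p. For assumed p of 5%, 10% and 20% this is 2, 4 and 8.
- Recorded per arm = 40 × p × c. With an assumed c of 0.5 in both arms this is 1, 2 and 4.
- Unrecorded over both arms = 2 × 40 × p × (1 − c) = 2 of 4, 4 of 8 and 8 of 16.
- Apparent risk ratio at equal true risk = c₁/c₂ = 0.5/0.5 = 1.0.

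A filter that works equally in both arms loses events but creates no spurious difference. A distorted ratio needs c₁ ≠ c₂, and nothing in the article supplies values for either.

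**The case against.** **The article condenses a longer protocol.** The amendment section says that the safety reporting period and responsibilities were clarified in June 2018, so the full protocol may name the assessor. That the article does not name one is therefore not a fault. The capture rule is different: the article states it, and it sits badly with the rule for non-serious events.

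**Study-related may loosely mean arising during the study.** This is possible. However, the same section uses related and relationship in the causal sense, and if the loose meaning was intended, the rewording is still needed.

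**The form's fields are not redundant.** This is correct. An event admitted as study-related may be due to the device, the operation or both, and the form separates these. It still cannot classify an event that was never admitted.

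**Other routes exist, and the Committee's data are described as including related AEs, which suggests a wider set.** This stands in part. It would be too strong to say that unrelated SAEs cannot reach the Committee: some may come to light through the notes review or the visit question. These remain partial substitutes.

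**No between-arm comparison of all-cause SAEs is specified.** This is also correct. The declared safety outcome is surgery-related complications. The point therefore rests on the by-arm review by the Committee and on safety reporting, not on a named test.

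**A stronger reading to avoid.** A reader might infer that the unblinded surgeon screens SAEs differently by implant and so biases the comparison. The documents do not support this. The surgeon is not given that role, and usual-care and outcome staff are blinded. The Surgical flow and training section says that surgeons completed a learning curve with the newer device until confident. Differential filtering is possible, but it is not shown.

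**Conclusion.** The point holds as one of incomplete capture. On its plain wording, the Safety section records serious events more narrowly than non-serious ones, and SAEs judged unrelated before recording may be missing from the by-arm data. This rests on reading study-related causally and on the full protocol, not shown, having no wider rule.

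The documents do not allow the number of lost events to be estimated; the counts in the working depend wholly on assumed rates. Bias between arms is not established. The primary Oxford Knee Score analysis is not affected. The label is cheap improvement.

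**What to change.** In the Safety section, replace the restriction to study-related SAEs with all SAEs from surgery to the end of follow-up. Record relationship to the device and to the procedure afterwards, as a classification of events already on the form. Leave the rules for onward reporting as they are. Give the Safety Committee all SAEs by arm, with related SAEs shown as a subset.

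It would help to state who classifies relatedness and whether that person knows the allocation. A classifier unaware of allocation would be a useful extra, but the main change does not depend on it.

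The cost is a wording change and a few more SAE forms for unrelated events among 80 patients followed for 6 months.
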